## Abstract

**Background:**

Schizophrenia, schizoaffective disorder, and bipolar affective disorder are debilitating psychiatric conditions characterized by a chronic pattern of emotional, behavioral, and cognitive disturbances. Shared psychopathology includes the pre-eminence of altered affective states, disorders of thoughts, and behavioral control. Additionally, those conditions share epidemiological traits, including significant cardiovascular, metabolic, infectious, and respiratory co-morbidities, resulting in reduced life expectancy of up to 25 years. Nutritional ketosis has been successfully used to treat a range of neurological disorders and preclinical data have convincingly shown potential for its use in animal models of psychotic disorders. More recent data from open clinical trials have pointed toward a dramatic reduction in psychotic, affective, and metabolic symptoms in both schizophrenia and bipolar affective disorder.

**Objectives:**

to investigate the effects of nutritional ketosis via a modified ketogenic diet (MKD) over 14 weeks in stable community patients with bipolar disorder, schizoaffective disorder, or schizophrenia.

**Design:**

A randomized placebo-controlled clinical trial of 100 non-hospitalized adult participants with a diagnosis of bipolar disorder, schizoaffective disorder, or schizophrenia who are capable of consenting and willing to change their diets.

**Intervention:**

Dietitian-led and medically supervised ketogenic diet compared to a diet following the Australian Guide to Healthy Eating for 14 weeks.

**Outcomes:**

The primary outcomes include psychiatric and cognitive measures, reported as symptom improvement and functional changes in the Positive and Negative Symptoms Scale (PANSS), Young Mania Rating Scale (YMS), Beck Depression Inventory (BDI), WHO Disability Schedule, Affect Lability Scale and the Cambridge Cognitive Battery. The secondary metabolic outcomes include changes in body weight, blood pressure, liver and kidney function tests, lipid profiles, and markers of insulin resistance. Ketone and glucose levels will be used to study the correlation between primary and secondary outcomes. Optional hair cortisol analysis will assess long-term stress and variations in fecal microbiome composition. Autonomic nervous system activity will be measured via wearable devices (OURA ring and EMBRACE wristband) in the form of skin conductance, oximetry, continuous pulse monitoring, respiratory rate, movement tracking, and sleep quality. Based on the encouraging results from established preclinical research, clinical data from other neurodevelopment disorders, and open trials in bipolar disorder and schizophrenia, we predict that the ketogenic metabolic therapy will be well tolerated and result in improved psychiatric and metabolic outcomes as well as global measures of social and community functioning. We additionally predict that a correlation may exist between the level of ketosis achieved and the metabolic, cognitive, and psychiatric outcomes in the intervention group.

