## Assessment of cognitive function

4

Cognitive functioning at baseline (T0) and post-intervention (week 14, [T3]) will be assessed using the Cambridge Neuropsychological Test Automated Battery (CANTAB). CANTAB measures are a reliable, valid, sensitive way of collecting comprehensive and accurate information on cognitive functioning in a clinical sample (58). Test batteries are delivered digitally using an iPad, allowing for standardized data collection at multiple time points and automated creation of comprehensive data sets. The level of information provided by each CANTAB measure allows for in-depth analysis of highly specific components of cognitive functioning providing specific insight into intervention efficacy within the context of a much wider dataset (59, 60). A customized test battery, consisting of 7 separate neuropsychological assessments (Table 4) was designed for data collection during this clinical trial.

**Table 4 tab4:** CANTAB neuropsychological test aspects.

Neuropsychological test (CANTAB)	Test variation	Administration time (Min)	Outcome measures
Motor Screening Task (MOT)	Voice	2	Accuracy Difficult/speed adjustment
Spatial Working Memory (SWM)	Recommend Standard Tone 2.0	4–6	Errors Incorrect selection, reselection
Emotional Recognition Task (ERT)	Short (Caucasian)	6–10	Correct recognition Response latency
Rapid Visual Processing (RVP)	1 Target Tone	7	Response latency Probability of false alarms sensitivity
Paired Associated Learning (PAL)	Recommended Standard Tone	8	number of errors number of trails required memory scores stages completed
One Touch Stocking of Cambridge (OTS)	Short	10	number solved on first choice Mean number of choices to solve Mean latencies
Cambridge Gambling Task (OTS)	Ascending First Shortened Tone	12–18	Risk-taking Decision-making quality Decision time Risk adjustment Delay aversion Impulsivity
Total administration time		49–61	

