### Sample size and statistical power

8.1

The optimal sample size is calculated based on a statistical power of 90% and a significance level of 0.05 (two-tail). To calculate the sample size, we have estimated the incidence of significant improvement in primary or secondary outcome measures to be 75% in group 1 (individuals on the KD) and 40% in group 2 (individuals on the AGHE diet). We will aim for a 1:1 enrolment ratio.

Using these values, our estimated sample size is 80 individuals (40:40), however, considering a dietary intervention attrition rate of at least 20%, we will aim to recruit 100 individuals (50:50).

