### Data analysis plan

8.2

The analysis of the biological samples will be conducted by biomedical staff at James Cook University overseen by the James Cook University Specialist in Clinical Biochemistry and Clinical Research Coordinator of the Australian Institute of Tropical Health and Medicine. This will follow standard analytic pipelines established in these units.

We predict that analyses of observed data will be largely descriptions of response, adherence, and distributions of values. Simple correlations between study parameters will follow standard statistical methods and the assistance of a statistician has been sought to define the statistical plan before the research plan is finalized. Software packages will include SPSS (v28) and *R* (v4.2.1).

In line with Burgess et al. (62) and many other modern statisticians who have described the procedure of hypothesis testing on baseline characteristics as unnecessary and potentially harmful (63), we will present the distribution of baseline information of intervention groups in a simple table, allowing readers to compare the extent of similarities, each with a mean and percentage value for both treatment groups separately. Additional co-variables may likely be at play, especially socioeconomic status, BMI, and severity of illness. Therefore, a degree of covariate adjustment is expected at the statistical calculation stage. Logistic regression and Analysis of Covariance are likely going to be incorporated into the data analysis plan.

For our quantitative endpoints (e.g., on psychiatric scales and metabolic parameters), linear mixed effects (LME) models will be used to compare the intervention and control groups. If normality cannot be assumed, a logarithmic transformation of the response variable will be performed to meet the assumption of normality. Mixed-effect logistic regression will be used for binary endpoints and longitudinal data. If data normality cannot be achieved, a comparison of our variables of interest between groups will take place using non-parametric tests, e.g., the Mann–Whitney U test. All analyses will be conducted by an intention-to-treat (ITT) approach using all available data, including those who were not to complete the study. Patient data will be analyzed per their original treatment allocation. All data analyses will be performed using 5% significance levels and audited by several members of the research team to ensure accuracy before submission.

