
Our trial design has some limitations. Firstly, despite our best efforts to keep the overseeing psychiatrists blind to the dietary arm allocation of individual participants, we cannot rule out the possibility that some participants may disclose their diets during the psychiatric assessments in the middle or at the end of the trial. Also, an argument can be made that some of our motivated participants may have information about the expected benefits of the ketogenic metabolic therapy in their condition, which could conceivably introduce an expectation bias if assigned to the ketogenic arm of the trial. We will, however, obtain their daily blood ketone levels which can be correlated with the results of the psychiatric and cognitive assessment, and give an objective control measure to address the above limitations. Another possible limitation is that due to the nature of this clinical trial conducted in an outpatient setting, relying on the ability of the participant to adhere to a relatively restrictive dietary regime independently, the recruited participants will be better functioning than some other patients with serious mental illness, resulting in a self-selected study population. We acknowledge this limitation, but we argue that although we might be able to demonstrate better adherence in this self-selected group, it may be a strength of the trial to demonstrate symptom improvement in participants who may be somewhat better functioning already. Additionally, demonstrating adherence to a restrictive dietary regimen by a population with severe mental disorders in the community may in itself be regarded as a satisfactory outcome measure.

In conclusion, we expect this randomized controlled clinical trial to assess the feasibility, efficacy, and safety of ketogenic metabolic therapy in schizophrenia and bipolar disorder. To our knowledge, our proposed trial is the first of its kind worldwide. We hypothesize that this study will reveal improvements in symptoms, overall quality of life, and better metabolic functioning for our participants. Results from this trial may inform future studies on more specific mechanisms of action, as well as introduce a novel treatment modality to manage psychiatric disorders that would otherwise have been considered as long-term, debilitating conditions.

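### Six unranked primary instruments, a 5% level for every analysis and a sample size built for one test: followed as written, the chance of at least one false positive primary result is up to about 26%, not 5%.

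*Protocol article*

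**What the plan says.** The abstract (Outcomes) sets the primary family: "The primary outcomes include psychiatric and cognitive measures, reported as symptom improvement and functional changes in the Positive and Negative Symptoms Scale (PANSS"), followed by "Young Mania Rating Scale (YMS), Beck Depression Inventory (BDI), WHO Disability Schedule, Affect Lability Scale and the Cambridge Cognitive Battery". That makes six instruments. The list puts none of them first and names no time point at which the primary comparison is made. Sections 3 and 4 describe the same instruments, again without ranking them. Section 2.1.2 has the psychiatric scales repeated at week 8 (T2) and week 14 (T3), and the cognitive tests repeated at week 14 only.

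Section 4 describes CANTAB as "A customized test battery, consisting of 7 separate neuropsychological assessments", and Table 4 lists several outcome measures for each test.

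Section 8.2 gives the error rule: "All data analyses will be performed using 5% significance levels".

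Section 8.1 makes one calculation, "based on a statistical power of 90% and a significance level of 0.05 (two-tail"), with the proportion improving taken "to be 75% in group 1 (individuals on the KD) and 40% in group 2 (individuals on the AGHE diet"). The event counted there is a significant improvement on a primary or a secondary measure, and it is not tied to any one instrument. The result is 80 participants, raised to 100 for attrition of at least 20%.

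**The concern.** These three statements do not fit together. A 5% level for each analysis controls the error of one primary comparison. Applied to six comparisons of equal standing, it does not control the chance that at least one of them is falsely positive. Nothing stated prevents the one significant instrument from being reported as the trial's primary result.

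Mixed results raise the same problem. If the BDI favoured the ketogenic diet and the PANSS showed nothing, the stated text would not tell a reader whether the trial had met its primary aim.

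This matters because the article presents the trial as a test of efficacy and, to the authors' knowledge, the first of its kind. A positive primary claim would carry weight, so its error rate should be the one stated.

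**Working it through.** **Inputs from the article.** Six primary instruments (abstract); 5% per analysis (Section 8.2); two-sided 0.05, 90% power, 75% against 40%, 1:1 allocation, 20% attrition (Section 8.1).

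**Assumption.** The article gives no correlation between the instruments. I take one common correlation for all pairs and show 0 to 0.8.

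**Step 1: reproduce the stated sample size.** Two proportions, pooled variance under the null, no continuity correction, mean proportion (0.75 + 0.40)/2 = 0.575:

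n per arm = [1.960 × √(2 × 0.575 × 0.425) + 1.282 × √(0.75 × 0.25 + 0.40 × 0.60)]² / 0.35² = 39.8, so 40.

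This gives 80 in total, and 80/0.8 = 100. Power at 40 per arm is 90.1%. The stated figures are reproduced with the whole 0.05 spent on one test, so no alpha is divided.

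**Step 2: family-wise error for six tests when no outcome is affected.**

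- Independent tests: 1 − 0.95⁶ = 0.265.
- Common correlation ρ, with c = 1.960: 1 − ∫ φ(u) [Φ((c − √ρ·u)/√(1−ρ)) − Φ((−c − √ρ·u)/√(1−ρ))]⁶ du, integrated numerically.

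| Assumed correlation | Chance of at least one false positive |
|---|---|
| 0 | 26.5% |
| 0.3 | 24.1% |
| 0.5 | 20.7% |
| 0.8 | 13.9% |

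Against the nominal 5%, this is an inflation of 26.5/5 = 5.3 times at the top of the range and 13.9/5 = 2.8 times at the bottom.

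**Step 3: count only false positives that favour the ketogenic diet.** Each test then carries 2.5%. Independent: 1 − 0.975⁶ = 14.1%. At correlation 0.5: 10.4%.

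**Step 4: illustrate the price of keeping six primaries.** The strictest equal split is 0.05/6 = 0.0083, with critical value 2.638. With the Section 8.1 proportions and 40 per arm:

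power = Φ([0.35 × √40 − 2.638 × √(2 × 0.575 × 0.425)] / √(0.75 × 0.25 + 0.40 × 0.60)) = Φ(0.565) = 71%.

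Restoring 90% at that level takes 59 per arm, 118 in total, and 118/0.8 = 147.5, so 148 recruited. Holm rejects everything that this equal split rejects, so 71% is a lower bound for the power of any one test under Holm.

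**The case against.** The strongest reply is that this is a journal article and a statistical analysis plan may exist. Section 8.2 says a statistician's help was sought in defining the plan, and a hierarchy or adjustment could well be there. That reply stands against any complaint that a hierarchy is missing, and none is made here. It does not answer the point about what is stated. The article itself chooses the primary set, applies 5% to all analyses and spends a full 0.05 in the sample size. A later plan that divided alpha across the six would have to depart from the last two. It is also true that the 5% sentence does not say whether it means per test or across the family. Per test is the natural reading; if the other was meant, the sentence should say so.

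A reader might infer more than the article supports, in four ways.

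- **That a false positive primary result is likely.** For six tests the range is 14% to 26%, and 14% at most if only errors favouring the ketogenic diet count. That is inflated, but well short of likely.
- **That there are 27 primary tests.** Table 4 can be read as 22 CANTAB measures (2 + 2 + 2 + 3 + 4 + 3 + 6), which with five scales makes 27; then 1 − 0.95²⁷ = 75% if independent, 48% at correlation 0.5 and 25% at 0.8. But the abstract lists the battery as one item, and no text says that each measure is a separate primary. The count also depends on how run-together cells such as "Risk-taking Decision-making quality Decision time Risk adjustment Delay aversion Impulsivity" are divided, and it includes the motor screening task.
- **That adherence is a further route to success.** The remark that it "may in itself be regarded as a satisfactory outcome measure" is hedged text in the Discussion. Adherence is not in the primary list, and no between-arm test of it is stated.
- **That PANSS and YMRS are each analysed in all diagnoses.** The article does not state the analysis population for either scale, and that would be a separate matter from multiplicity.

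**Conclusion.** The point holds for the six stated instruments. With the 5% rule applied to each, the family-wise error is up to about 26%, about 21% at an assumed correlation of 0.5 and about 14% at 0.8. These figures assume that the diet affects none of the six, that each instrument gives one test, and that the instruments share a common non-negative correlation, which the article does not report. The error rises if CANTAB measures are tested separately as primaries, by an amount the article does not fix.

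The stated 80 participants (100 with attrition) support one primary test at 90% power. The 71% figure is an illustration only: it rests on a binary event that Section 8.1 ties to no scale, whereas Section 8.2 analyses the scales as quantitative endpoints with mixed models.

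**What to change.** Make one of two changes in the abstract and Sections 8.1 and 8.2 before any unblinded analysis, since a primary endpoint chosen afterwards would not be credible.

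1. **One primary.** Name a single primary endpoint at T3, tested at two-sided 5%, and make the other instruments secondary. Tie the Section 8.1 calculation to that endpoint. If the 75% and 40% can be justified for it as a binary response, 80 and 100 stand; if it is a quantitative scale, the calculation has to be redone for that scale.
2. **Six primaries.** Replace the blanket 5% sentence with Holm across the six at a family-wise 5%. Let CANTAB enter as one pre-specified measure, and restate the power.

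Both options need only changes of wording in the protocol and analysis plan, and an update of the trial's registration if its primary outcomes match the abstract. The first costs the right to call several results primary. The second costs power per instrument at the planned size (in the illustration above, not below about 71% against the stated 90%) or a larger sample to recover it.

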Pre-existing psychiatric and metabolic treatment will continue as per the treating team’s medical advice. Metabolic medication might be adjusted for those in the KD group in collaboration with their physician to minimize the risk of hypoglycemia. Participants in both groups will be given a blood ketone and glucose monitoring device at the end of the enrolment visit (T1) and instructed to take a daily capillary blood sample to measure glucose and ketone levels. The measurement will occur consistently every day, 2 h before their routine dinner time. Daily glucose and ketone measurements are uploaded to a team’s database daily and strictly monitored to detect any emergent metabolic abnormality.

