In case of demonstrated efficacy, it is crucial to understand the mechanism of action of this novel metabolic intervention to give informed advice to the psychiatric community on any potential change in clinical practice. Our trial will collect data from different domains, including systemic metabolism and inflammatory processes, autonomic nervous system activity, sleep patterns, and changes in the gut microbiome. Outcome measures from these systems, when correlated with improved psychiatric symptoms, cognitive functions, and overall daily functioning will inform us about the potential involvement of underlying mechanisms. With regards to mechanisms of action of dietary intervention, the possible mediating role of the gut microbiome is of primary importance as the ecosystem of the bacteria in the gastrointestinal system interacts with the consumed diet even before the different nutrients and other food-derived molecules get into the bloodstream (64–67). It is conceivable that some of the effects of the ketogenic metabolic therapy may be mediated by the gut microbiome, either directly through microbiome-derived metabolites that reach the brain or indirectly through changes in the enteric nervous system activity. We aim to establish such a role for the gut microbiome by demonstrating ketogenic diet-related changes associated with symptom improvement. Ketone bodies, beta-hydroxybutyrate, and acetoacetate are the metabolic products of the liver while on the ketogenic diet (36). Ketones have been shown to directly benefit brain bioenergetics (68, 69). The daily ketone monitoring will make it possible not only to confirm adherence to the ketogenic diet but also to correlate ketone levels with daily changes in the self-reported energy levels of the participants. Alterations in autonomic nervous system activity and sleep have been widely reported in schizophrenia (70) and bipolar disorders (71, 72). The ketogenic diet seems to be effective in influencing these functions. Therefore, the potential mechanistically important role of autonomic nervous system activity and sleep health can be uncovered by monitoring these functions using wearable devices before the introduction and at the end of the dietary intervention. Although human studies are rarely designed to include an experimental intervention that directly informs about exact mechanisms of action, the complex analysis of multiple, interacting systems will show biomarkers that are specifically modified by the treatment and associated with improvements in different symptom domains.

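### Achieved ketosis within the ketogenic arm is non-randomised adherence, so a simple ketone–outcome correlation could be significant without any ketosis effect and cannot serve as a control for unblinding or expectation bias

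*Protocol article*

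**What the plan says.** The Abstract (Outcomes) adds to the main efficacy prediction that "a correlation may exist between the level of ketosis achieved and the metabolic, cognitive, and psychiatric outcomes in the intervention group". This association lies inside one randomised arm.

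Section 8.2 (Data analysis plan) gives the only method stated for associations: "Simple correlations between study parameters will follow standard statistical methods". The next paragraph of that section notes "Additional co-variables may likely be at play, especially socioeconomic status, BMI, and severity of illness" and says that "a degree of covariate adjustment is expected at the statistical calculation stage". That paragraph concerns the baseline comparability of the two diet groups and does not mention ketones.

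Under section 2.1.2 (Assessments), participants in both arms are "instructed to take a daily capillary blood sample to measure glucose and ketone levels". The Discussion treats these readings as an adherence measure: "The daily ketone monitoring will make it possible not only to confirm adherence to the ketogenic diet". It also describes the outpatient trial as "relying on the ability of the participant to adhere to a relatively restrictive dietary regime independently".

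Among the limitations, the Discussion accepts that assessors may be unblinded and that motivated participants may expect benefit from the ketogenic diet. Its answer is that daily ketones can be "correlated with the results of the psychiatric and cognitive assessment, and give an objective control measure to address the above limitations".

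**The concern.** Randomisation makes the two arms comparable. It does not make high-ketone and low-ketone participants within the ketogenic arm comparable, because ketone level there depends on behaviour after randomisation. Three routes could produce an association without any effect of ketosis:

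- **Baseline severity:** more severely ill participants may adhere less and also score worse at T3.
- **Expectation or motivation:** a participant who believes in the diet may adhere better and also rate themselves better on self-report scales such as the BDI and WHODAS 2.0.
- **Lapse on worsening:** a participant whose symptoms worsen may stop keeping to the diet, so low ketones follow the bad outcome.

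The second route matters most for the Discussion. Expectation is one of the biases the ketone correlation is meant to address, yet expectation can itself create that correlation. A positive result could then be read as support for the trial against the very bias that produced it.

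**Working it through.** **1. Size of the arm.** The documents give 75% vs 40%, 90% power and two-sided 5% (section 8.1). With mean proportion 0.575, n per arm = [1.96·√(2·0.575·0.425) + 1.2816·√(0.75·0.25 + 0.40·0.60)]² / 0.35² = (1.370 + 0.838)² / 0.1225 = 39.8, so 40. That is 80 in total, and 80/0.8 = 100. The stated figures reproduce. They place 40 to 50 people in the ketogenic arm. The article gives no power figure for the ketone association.

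**2. Threshold for significance.** |r| must exceed t/√(n−2+t²). For n = 40, t = 2.024 gives 0.312. For n = 50, t = 2.011 gives 0.279.

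**3. Common cause, no ketosis effect.** Suppose severity correlates a with lower ketones and a with a worse outcome. The expected spurious correlation is a². The chance of significance is approximately 1 − Φ(1.96 − atanh(a²)·√(n−3)). For a = 0.5 and n = 40: atanh(0.25)·√37 = 0.2554 × 6.083 = 1.554, and 1 − Φ(0.406) = 34%. Simulation (20,000 runs per row) gives:

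| a on each path | a² | n = 40 | n = 50 |
|---|---|---|---|
| 0.3 | 0.09 | 8.6% | 9.8% |
| 0.4 | 0.16 | 17% | 21% |
| 0.5 | 0.25 | 35% | 42% |
| 0.6 | 0.36 | 64% | 74% |
| 0.7 | 0.49 | 91% | 96% |

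Adjusting for a perfectly measured severity covariate restores about 5% in every row. A separate check with severity paths of 0.3 to 0.5 gave 17% to 33% unadjusted and 5% after adjusting for the T1 value.

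**4. Lapse on worsening, no ketosis effect.** If worsening lowers ketones with correlation 0.3, 0.5 or 0.7, a simple correlation at n = 40 is significant in 48%, 92% and about 100% of trials. Adjusting for baseline severity still leaves 43%, 83% and 98%. The adjustment mentioned in section 8.2, even if applied here, would not close this route.

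**5. Change scores.** With both routes at 0.3 and n = 40, differently built two-period models gave 34% to 73% for correlations with the final score, but only 8% to 15% for change from baseline. On change scores the severity route runs the other way, because sicker participants have more room to improve. The two routes partly cancel and could bring the rate close to nominal. Acting alone they do not cancel: in one such model the severity route (0.2 to 0.5) gave 9% to 32% on change scores, and the lapse route (0.3) gave 37%.

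**6. Whether to adjust for the T2 outcome.** T2 is measured after the T1–T2 ketones and lies on the path from early ketosis to T3. With a true ketosis effect of 0.3 and n = 40, early ketones adjusted for T1 detected it in 64% of runs. Adding T2 cut this to 18%. I reproduced both figures within simulation error, assuming a visit-to-visit correlation of 0.7 and half the ketone variance common to both periods.

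**7. What T1 adjustment leaves open.** Suppose worsening between T1 and T2 lowers ketones in that interval with coefficient 0.3, and scores correlate 0.7 between visits. The partial correlation of early ketones with T3 given T1 is (0.3/√1.09)·(0.7/√1.49) = 0.287 × 0.573 = 0.165. Then atanh(0.165)·√36 = 1.00 and 1 − Φ(0.96) ≈ 17%. The T2-adjusted version stays at 4% to 5% under this route, which is why it belongs as a sensitivity analysis. It does not deal with an unmeasured stable cause: one acting at 0.3 to 0.5 on both ketones and symptoms gave 10% to 21%.

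**The case against.** The prediction is hedged and names no test. The sentence on simple correlations is general and does not mention ketones. The same section says that a statistician's help has been sought, expects some covariate adjustment with severity among the candidates, and uses mixed models for the quantitative endpoints. Details of an additional association can properly be left to an analysis plan that is not shown. Eligibility requires clinical stability and willingness to adhere, which may narrow the spread of severity. The Abstract also speaks of improvement and change, for which step 5 shows much less inflation when both routes act.

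Much of this stands, and it limits what can be claimed. A reader might infer that the trial would report a false dose-response. The documents do not support that: they never use the term, and the direction and size of any bias rest on strengths they do not give. A reader might also infer that ketones will be averaged over the whole trial. No ketone summary is stated; section 7.4 mentions only time spent in ketosis. Nor does the remark about participants' ability to adhere say that sicker participants in the ketogenic arm will adhere less. It concerns selection of the whole sample.

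What the objection does not remove is the text itself. The only method named for associations is simple correlation, the covariate sentence is not tied to the ketone data, and the Discussion gives the correlation a bias-control role. That role is stated in the article, not left to a later plan.

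**Conclusion.** The point holds as a limit on interpretation. Analysed by simple correlation, the within-arm association could be significant with no ketosis effect, so it cannot rule out unblinding or expectation bias. For 40 participants the illustrative false-positive rate is about 9% to 35% for a common cause at 0.3 to 0.5, and about 48% for lapse on worsening at 0.3. It is lower on change scores when both routes act. All these strengths are assumptions.

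It would be wrong to conclude that the trial's main result is compromised. The between-arm comparison is by allocated group on an intention-to-treat basis and does not use achieved ketosis.

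**What to change.** 1. Replace the simple correlation with a regression, in the ketogenic arm, of each T3 outcome on mean ketone level between T1 and T2, adjusted for the T1 value of that outcome and diagnosis.
2. Do not adjust for the T2 outcome in the main version. Show that version as a sensitivity analysis for psychiatric and metabolic outcomes. Cognition is not measured at T2, so only the baseline-adjusted version is available there.
3. Report the results as exploratory, observational associations and not as a dose-response.
4. Withdraw the statement in the Discussion that the ketone correlation is an objective control for the blinding and expectation limitations.

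The cost is wording and one regression per outcome, on data already collected. Ketones after T2 are not used as exposure, which loses some power, more so the less early ketones predict later ones. Lapse on worsening before T2 is not fully removed (step 7), and a stable unmeasured cause such as motivation remains uncontrolled. The observational label is therefore needed even after the change.
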